### The SMARThealth programme

The George Institute for Global Health developed the Systematic Medical Appraisal, Referral and Treatment programme for cardiovascular disease prevention and management (SMARThealth) [20]. This global programme draws on innovative mobile-health technologies to promote evidence-based, clinical decision support systems. SMARThealth takes a health care ‘eco-system’ approach: (i) strengthening the capacity of primary health care workers and local communities; (ii) delivering fit-for-purpose electronic decision support systems and supportive technologies for self-management; and (iii) integrating with existing health system infrastructure. SMARThealth strengthens the skills of community health workers, known as ASHA (Accredited Social Health Activists) in India, to perform risk assessments for various conditions using an app deployed on a low-cost Android tablet. Data are stored securely on a cloud-based server with offline capabilities in areas of limited network connectivity. People at elevated risk of the screened conditions are electronically referred to the Primary Health Centre (PHC) for medical review. The PHC doctor has a complementary tablet app which communicates with the secure server and is provided with more complex decision support, including suggested medication management, based on national and international guidelines [21–25].

We have adapted the SMARThealth approach to improve the community-level identification, diagnosis, referral and management of women with anaemia, diabetes and hypertension during pregnancy and in the year after birth (SMARThealth Pregnancy) [26]. We demonstrated the acceptability and feasibility of SMARThealth Pregnancy in a pilot cluster randomised trial in four sites in rural India during 2019–2020 involving 200 pregnant women and 50 frontline health workers (unpublished work).

The SMARThealth Pregnancy programme evaluates both clinical and implementation effectiveness. A separate protocol will be published on the process evaluation, with detailed implementation outcomes and strategies.

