#### Eligibility for women

Up to 5000 pregnant women will be screened until the sample size has been reached. Potentially eligible women will be identified by ANMs and ASHAs with the support of laboratory technicians. Women will be eligible if they are ≥ 18 years old. Women can be enrolled at any time during the pregnancy at or after 12 weeks of gestation, as determined by ultrasound scan, date of last menstrual period or best clinical estimate.

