### Relevant concomitant care permitted or prohibited during the trial {11d}

This is a pragmatic trial; hence, women will be free to attend any other health providers (including private health providers, traditional medicine practitioners and care providers from other government facilities) to seek additional care. These health utilisation patterns will be captured as part of the process evaluation.

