#### Secondary outcomes

Secondary outcomes will be collected across four areas:Implementation outcomesClinical endpointsClinical service delivery indicatorsWomen’s wellbeing and mental health

(1) Implementation outcomes

Using the RE-AIM framework [31], we will report the following implementation outcomes (Table 1):

**Table 1 Tab1:** Implementation outcomes to be assessed

RE-AIM dimension	Definition	Assessment measure	Data source	Timepoint
**Reach**	The number of people and percent of the target population who are impacted, and the extent to which those reached are representative and include those at most risk	Size of the target population	PHC records	Study end
		Number of women enrolled in the study and the number receiving the intervention	SHP app	Study end
		Comparison of characteristics of the individuals enrolled in the study to the target population	SHP app; district records	Study end
**Effectiveness**	A measure of the impact on health individual-level primary outcome including positive, negative and unintended consequences	The proportion of women with anaemia as measured by capillary test at 12 months after birth The proportion of women with follow-up blood pressure measurement or blood glucose tests during the 12 months after birth following a pregnancy affected hypertension or diabetes	Endline CRF	Study end
		The proportion of screening visits performed per protocol (maximum 7 SHP visits) The proportion of visits conducted in person and by phone The proportion of visits performed at the stated time in the protocol	Intervention group only: SHP app	Study end
		Self-report rating of health outcome (WHO-5 quality of life)	Endline CRF	Study end
		Self-report rating of health behaviour (WHO infant feeding questionnaire)	Endline CRF	Study end
		Quantitative comparison of outcomes across subgroups (family income, caste stratification, parity, rural/semi-rural, private/ government delivery) with qualitative exploration	Endline CRF, interviews and FGDs	Study end
**Adoption**	The number and percent of settings/providers/interventionists who participate, and the extent to which these are representative of those who the target population will use or visit	Number of PHCs invited and the number that participate at the start of the study	Baseline study information	Study initiation
		Number of participating PHCs at the end of the study	Endline study information	Study end

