### Participant timeline {13}

PHCs will be recruited and randomised before individual participant recruitment commences. After randomisation, ASHAs in the intervention clusters will attend the education programme to receive training on the clinical conditions, use of the point-of-care devices and SMARThealth Pregnancy app. Individual participants will be approached by their ASHA worker to participate after 12 weeks’ gestation. If they consent to participate in the study, a study team member will complete a baseline assessment, which includes questionnaires, blood pressure and haemoglobin measurement. A study team member will perform a mid-point assessment between 9 and 12 weeks after birth to capture events and healthcare utilisation including out-of-pocket costs around the time of birth. A study team member will conduct the final study visit 9–12 months after delivery, which will involve completing questionnaires, and measuring haemoglobin and blood pressure (Table 2).

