#### Variability in the primary outcome and estimated effect size

The pilot study’s prevalence of anaemia during pregnancy was higher than the reported national levels, likely due to selection differences and differences in testing techniques (venous sample vs POC device used in the pilot study).

The prevalence of anaemia is slightly higher in non-pregnant than pregnant women (national estimate for India 53 and 50% respectively, NFHS 5 [39]). The national target for anaemia reduction is three percentage points per year as part of the Anaemia Mukt Bharat programme [18].

We estimate that our intervention will improve anaemia rates in these populations by 9% over 3 years (i.e. 53 to 44%). Determining a minimally clinically important threshold for anaemia is challenging. We selected the target decrease in anaemia as it was in keeping with the AMB programme [18], and to be an achievable and programmatically meaningful target with optimal support for anaemia prevention. Whilst anaemia is anticipated to decrease in the population because of the ongoing government programmes (including AMB), evidence from our pilot study is that compliance and implementation issues exist on the ground. Our intervention was designed to enhance delivery of the government programme and reaching of national anaemia reduction targets.

Given 30 clusters and an ICC of 0.02, 86 women per cluster are needed to detect a 9% absolute reduction (53 to 44%) with 80% power (a total sample size of 2580). Allowing for losses to follow-up of 20%, a sample size of 108 women per cluster is needed (a total sample size of 3240).

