## Statistical methods

### Statistical methods for primary and secondary outcomes {20a}

The primary analysis will be by intention to treat conducted at the participant level, using either random-effects models or generalised estimating equations adjusted for PHC clustering. We used a matched-pair design to balance cluster characteristics prior to randomisation, as recommended for community-based trials with a limited number of clusters [40]. Given the relatively small number of clusters, the analysis will not adjust for matching since this has been shown to provide unbiased estimates of the randomised intervention effect [41] and provide similar power to a matched analysis [40]. An unmatched analysis has the advantage that it can easily be conducted using participant-level data whilst allowing estimation of the intra-class correlation coefficient.

The final analysis is anticipated to occur 36 months after recruitment of the first participant. For the groups to be declared significantly different, the *P* value for the primary outcome must be ≤ 0.05. We will report the point estimate and confidence interval and present an assessment of the clinical relevance of our findings.

Baseline data will be presented for both groups. Continuous variables will be assessed for distribution, with appropriate statistical transformation (e.g. log or cubic splines) to correct for non-normality. Subgroup analyses will be performed by study location (Telangana or Haryana) to explore the effects of contextual factors on outcomes of interest. A detailed statistical analysis plan will be developed and publicly available before unblinding.

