### Methods for additional analyses (e.g. subgroup analyses) {20b}

Subgroup analyses will be performed for women with GDM and HDP separately and with both conditions. The analysis of secondary outcomes will be performed on all women reaching the study endpoint. A structured observation of health worker performance will be performed on a subsample of 200 women from 10 intervention and control PHC facilities to assess fidelity to the study intervention.

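### Table 1 lists private/government delivery as an outcome subgroup, but delivery sector is settled after randomisation and antenatal exposure, so arm differences within it are not randomised comparisons

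*Protocol article*

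**What the plan says.** Table 1 (Outcomes {12}, Secondary outcomes) gives as one Effectiveness measure: "Quantitative comparison of outcomes across subgroups (family income, caste stratification, parity, rural/semi-rural, private/ government delivery) with qualitative exploration". The table defines Effectiveness as impact on the individual-level health outcome. Nothing in the row sets delivery sector apart from the other four factors or calls the comparison descriptive.

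The order of events is given elsewhere:

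- Participant timeline {13}: "PHCs will be recruited and randomised before individual participant recruitment commences".
- Eligibility for women: "Women can be enrolled at any time during the pregnancy at or after 12 weeks of gestation".
- Intervention description {11a}: ASHAs assess women during pregnancy as well as in the year after birth, and the app can refer a woman to the PHC physician. The SMARThealth programme section describes the same route: "People at elevated risk of the screened conditions are electronically referred to the Primary Health Centre (PHC) for medical review".
- Relevant concomitant care {11d}: "women will be free to attend any other health providers", private ones included.

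The statistical sections name other subgroups. Section {20a} says "Subgroup analyses will be performed by study location (Telangana or Haryana) to explore the effects of contextual factors on outcomes of interest", and section {20b} says "Subgroup analyses will be performed for women with GDM and HDP separately and with both conditions". Delivery sector appears in neither.

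**The concern.** A subgroup supports a randomised estimate of effect modification only if treatment cannot influence membership. Four of the five factors meet that condition, because they describe the woman or her setting before exposure. Delivery sector does not. By the time it is known, women in intervention PHCs have had extra ASHA contact, point-of-care screening and possible referral into a government facility. If that alters who delivers where, the private stratum in one arm holds a different kind of woman from the private stratum in the other.

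An apparent difference in effect between sectors could then be selection alone. The Discussion says the implementation analyses will inform scale-up and wider adoption, so such an artefact could be mistaken for evidence on where the programme works.

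**Working it through.** **The plan's own figure.** The only related number is the sample size, where the closing percentage is the power: "Given 30 clusters and an ICC of 0.02, 86 women per cluster are needed to detect a 9% absolute reduction (53 to 44%) with 80%". Taking two-sided alpha of 0.05 (sidedness assumed), the unpooled two-proportion formula gives 481 women per arm before clustering. With 15 clusters per arm, m = 481 × 0.98 / (15 - 481 × 0.02) = 471.38 / 5.38 = 87.6, so 88 per cluster against the stated 86. At m = 86 the design effect is 1 + 85 × 0.02 = 2.7, the effective size is 15 × 86 / 2.7 = 477.8 per arm, and power is 79.6% (pooled) to 79.8% (unpooled). Allowing for loss, 86 / 0.8 = 107.5, so 108 per cluster, and 108 × 30 = 3240. The stated figure is reproduced within two women per cluster, and the present point does not depend on it.

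**The two readings of the row.** If outcomes are compared between women who delivered privately and women who delivered in government facilities, nothing was randomised between those groups. If arms are compared within each sector, the analysis conditions on a variable that arises after randomisation. Neither reading gives a randomised contrast.

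**Size, under assumed inputs.** The article gives no share of private deliveries, no anaemia prevalence by sector and no estimate of any shift, so every input below is an assumption. Suppose there is no true effect. In control, a share P = 0.30 delivers privately and G = 0.70 in government facilities. A share s of all women would deliver privately under control but in government facilities under intervention (movers). Anaemia risk is 45% in women who deliver privately in either arm, 56% in women who deliver in government facilities in either arm, and r in movers. The intervention-minus-control differences are:

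- Private stratum: -(s / P) × (r - 0.45)
- Government stratum: (s / (G + s)) × (r - 0.56)

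| s | r | Private (points) | Government (points) |
|---|---|---|---|
| 0 | any | 0 | 0 |
| 5% | 45% | 0 | -0.7 |
| 5% | 56% | -1.8 | 0 |
| 5% | 65% | -3.3 | +0.6 |
| 10% | 45% | 0 | -1.4 |
| 10% | 56% | -3.7 | 0 |
| 10% | 65% | -6.7 | +1.1 |

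For the last row: -(0.10 / 0.30) × 0.20 = -6.7 points, and (0.10 / 0.80) × 0.09 = +1.1 points. Overall prevalence in that row is the same in both arms. Control is 0.20 × 0.45 + 0.10 × 0.65 + 0.70 × 0.56 = 54.7%, and intervention sums the same three terms. The whole-arm comparison is therefore untouched.

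**Second set of assumptions.** Take 40% private deliveries in control at 45% anaemia and 53% overall, so government prevalence is (0.53 - 0.18) / 0.60 = 58.3%. Move 10% of all women, which is a quarter of private deliveries. Private prevalence under intervention is (0.18 - 0.10r) / 0.30: 45.0% if r = 45%, 43.3% if r = 50% and 40.0% if r = 60%, a spurious fall of 0 to 5.0 points. Government prevalence is (0.35 + 0.10r) / 0.70: 56.4% if r = 45% and 58.6% if r = 60%, a change of -1.9 to +0.2 points.

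**The case against.** The row is an implementation measure paired with interviews and focus groups. It does not say that treatment effects will be estimated within delivery sector or that an interaction will be tested, and delivery sector is not among the subgroups in {20a} or {20b}. A reader might infer that the trial intends to present a sector difference as a causal or confirmatory finding. The text does not support that: a purely descriptive comparison fits the wording as well. Modelling details may properly be left to the separate process-evaluation protocol and the statistical analysis plan. This limits the weight of the point but does not remove it, because the article itself places the variable among baseline factors under a heading about impact.

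A reader might also infer that the intervention does shift place of delivery. The article does not show this. Referral is for medical review, not for delivery, and free choice of provider applies in both arms. A shift is plausible and no more.

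The illustration is open to fair criticism as well. Its inputs are invented, and its largest values need movers more anaemic than the government group they join. Distortion in the larger government stratum is small. The 9-point target belongs to the primary outcome, which is not affected.

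Finally, because the row gives the endline CRF as a source, a reader might suspect that income would be taken at endline. That cell can simply refer to where the outcomes are recorded, and the timeline places questionnaires at baseline too, so no error is shown.

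**Conclusion.** The point holds in a limited form. Delivery sector is a post-randomisation, post-exposure variable listed beside four pre-exposure ones, and arm differences within it are not protected by randomisation. That conclusion rests on the timing in the article and needs no numerical assumption.

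The size of any bias does rest on assumptions. It is zero in both strata if nobody changes sector, and zero in a given stratum if movers carry the same risk as the other women in it. Otherwise it could reach a few points in the private stratum (0 to -6.7 under the first set of inputs, 0 to -5.0 under the second) and about two points or less in the government stratum. The direction is not fixed: movers at lower risk than those who stay, or a shift towards private care, would change the pattern.

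This is a minor point about one exploratory measure. The primary analysis, the sample size and the subgroups named in {20a} and {20b} are outside its scope.

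**What to change.** In Table 1, or in the analysis plan that implements it:

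1. Limit the effect-modification subgroups in this row to income, caste, parity and rural/semi-rural setting, as baseline characteristics.
2. Report place of delivery by arm as a process measure. The visit at 9 to 12 weeks after birth already captures events and healthcare use around the birth, so this should need no new data collection. The numbers by arm would also show whether any shift occurred.
3. If outcomes are still shown by delivery sector, label that comparison as descriptive and non-causal.

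The cost is a line or two of text and the loss of one exploratory subgroup-effect estimate. A new baseline question on intended place of delivery is not recommended: recruitment began on 1 July 2022, so it could not be put at baseline to women already enrolled.

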### Outcomes {12}

#### Primary outcome

The primary outcome will be the difference in the proportion of participants with anaemia, defined as haemoglobin measured using a point-of-care test < 12 g/dL at 12 months after delivery between the intervention and EUC clusters. Anaemia has been chosen as the primary outcome as it is the most common condition affecting women during pregnancy and breastfeeding across India. Measurement using a point-of-care device was chosen as this has been recommended in national guidelines and is a common method for diagnosing anaemia in rural settings, thereby reflecting real-world practice. The measurement will be performed by a member of the study team.

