*Implementation*: Fidelity to the intervention protocol for the trial and for the intervention itself and any adaptations during the trial. This will be measured assessing data completeness, and through qualitative methods with health workers.
*Maintenance*: We will explore the system-level factors needed for institutionalisation of the intervention and level of intent to continue to programme in the study settings and more widely using key stakeholder interviews and focus group discussions, as well as policy discourse analysis around maternal health and digital health policy.

(2)Clinical endpoints
*Anaemia*: Haemoglobin will be compared between intervention and EUC clusters as a continuous variable (measured in grams per decilitre on point-of-care test) and as categories of anaemia using the WHO thresholds used for non-pregnant adults: no anaemia > 12.0 g/dL; mild anaemia 11.0–11.9 g/dL; moderate anaemia 8.0–10.9 g/dL; severe anaemia < 8 g/dL
*Diabetes*: Between the intervention and EUC, we will compare venous blood glucose following a 2-h, 75-g oral glucose challenge at 1 year after birth in participants diagnosed with GDM during pregnancy. Blood glucose will be assessed as a continuous measure (in milligrams per decilitre) and as categories of glucose impairment: Normal: < 140 mg/dl, impaired glucose tolerance (IGT): 140–199mg/dl, Diabetes: ≥ 200 mg/dl
*Hypertension*: Blood pressure (BP) will be compared between women who developed HDP. BP will be assessed as a continuous measure (systolic, diastolic and mean arterial pressure) in millimetres of mercury (mmHg) using a validated sphygmomanometer and as a binary category of hypertension (yes/no) defined as BP > 140/90 mmHg(3)Clinical service delivery indicators
*Quality-of-care score*: We will measure differences between the intervention and EUC clusters using a quality-of-care score we have developed specifically for this study. The score comprises an equally weighted composite of clinical outcomes (anaemia, diabetes, hypertension) with measures of access and health professional visit frequency during pregnancy and in the first 12 months after delivery.

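### The secondary haemoglobin bands leave a reading of exactly 12.0 g/dL in no category, because the no-anaemia band is printed as above 12.0 instead of 12.0 and above

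*Protocol article*

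**What the plan says.** Under Outcomes {12}, Primary outcome, anaemia is "defined as haemoglobin measured using a point-of-care test < 12 g/dL at 12 months after delivery". A reading of 12.0 is therefore not anaemic.

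Under Secondary outcomes, (2) Clinical endpoints, haemoglobin is analysed in two ways. The first is continuous: "Haemoglobin will be compared between intervention and EUC clusters as a continuous variable". The second is "as categories of anaemia using the WHO thresholds used for non-pregnant adults", with the bands printed as "no anaemia > 12.0 g/dL; mild anaemia 11.0–11.9 g/dL" and then "moderate anaemia 8.0–10.9 g/dL; severe anaemia < 8 g/dL".

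The protocol gives no haemoglobin SD, no resolution for the point-of-care device, and no expected share of women at 12.0. It does not say what happens to a reading that fits no band.

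**The concern.** A set of outcome categories should place every possible value in exactly one band. Here a reading of 12.0 is too low for the no-anaemia band, which starts above 12.0, and too high for the mild band, which stops at 11.9.

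The value that falls through is the trial's own primary threshold. The planning prevalences of 53% and 44% below 12 put that threshold near the middle of the distribution in both arms, where readings are densest. The number of women affected is therefore unlikely to be trivial.

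At stake is the coherence of one secondary table. Someone coding the bands as printed would find women with a valid haemoglobin and no category. The four percentages would then either sum to less than 100% or be taken over a smaller denominator than the primary result.

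**Working it through.** **1. Coverage of the bands, at one decimal.**

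| Reading (g/dL) | Primary definition (< 12) | Secondary band as printed |
|---|---|---|
| up to 7.9 | anaemic | severe |
| 8.0 to 10.9 | anaemic | moderate |
| 11.0 to 11.9 | anaemic | mild |
| 12.0 | not anaemic | none |
| 12.1 and above | not anaemic | no anaemia |

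The joins at 7.9/8.0 and 10.9/11.0 have no gap. The mild, moderate and severe bands together hold exactly the readings below 12. The only uncovered value is 12.0.

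**2. Is it an artefact of text extraction?** No. The diabetes item in the same list prints its upper category correctly with ≥ (at 200 mg/dL), so the symbol survives there.

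**3. The plan's own denominator.** The sample size section states "Given 30 clusters and an ICC of 0.02, 86 women per cluster are needed". The planned contrast there is 53% against 44%, at 80% power.
- 30 × 86 = 2580, or 15 × 86 = 1290 per arm.
- Design effect: 1 + (86 − 1) × 0.02 = 2.70. Effective n per arm: 1290 / 2.70 = 477.8.
- SE = √[(0.53 × 0.47 + 0.44 × 0.56) / 477.8] = √(0.4955 / 477.8) = 0.0322.
- Power at two-sided 0.05 (sidedness is assumed; the protocol does not state it): Φ(0.09 / 0.0322 − 1.96) = 79.8%.
- With 20% loss: 86 / 0.80 = 107.5, rounded up to 108; 108 × 30 = 3240.

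The stated figures reproduce to within rounding. None of them uses the secondary bands.

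**4. Share of women at exactly 12.0.** The assumptions, none of them in the protocol, are normally distributed haemoglobin, readings rounded to 0.1 g/dL, and an SD between 1.0 and 2.0 g/dL. The mean is set so that the recorded proportion below 12 equals the planning prevalence p:

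μ = 11.95 − SD × Φ⁻¹(p)

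share = Φ((12.05 − μ)/SD) − Φ((11.95 − μ)/SD)

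| SD (g/dL) | Share, p = 53% | Share, p = 44% | Women of 2580 |
|---|---|---|---|
| 1.00 | 3.96% | 3.97% | 102 |
| 1.25 | 3.17% | 3.17% | 82 |
| 1.50 | 2.64% | 2.64% | 68 |
| 1.75 | 2.27% | 2.26% | 58 |
| 2.00 | 1.98% | 1.98% | 51 |

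The two arms differ by at most 0.01 of a percentage point.

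**5. Effect on the between-arm contrast if these women were left out of the table's denominator.** This is a hypothetical; the protocol does not prescribe it.
- Share 4.0%: 53 / 0.96 = 55.2% and 44 / 0.96 = 45.8%, difference 9.4 points.
- Share 2.0%: 53 / 0.98 = 54.1% and 44 / 0.98 = 44.9%, difference 9.2 points.

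Against the planned 9 points, the contrast moves by 0.2 to 0.4 of a point. Each arm's level moves by about 1 to 2 points.

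**The case against.** The best reply is that this is a typographical slip whose meaning can be recovered. The mild band is capped at 11.9 and the primary definition excludes 12.0 from anaemia, so only the no-anaemia band can consistently hold that reading. The article uses the strict sign loosely elsewhere: the abstract asks for more than one medical officer and more than two community health workers, where the eligibility criteria for primary health centres ask for at least one and at least two. A detailed public analysis plan is also promised before unblinding (Statistical methods {20a}), and band coding would normally be settled there.

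Most of this stands. It shows that the correction is uncontroversial and that harm is unlikely. It does not make the printed endpoint definition right, and a plan that copied the bands would carry the gap forward.

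A reader might infer more than the protocol supports, in three ways:

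- **That these women are dropped from the trial's anaemia analysis.** No section says so. They remain in the primary analysis, as not anaemic, and in the continuous comparison.
- **That secondary anaemia prevalence would exceed the primary result because 12.0 is coded as mild.** That would contradict the printed 11.9 cap as well as the primary definition. As printed, the count of anaemic women across the bands equals the primary count.
- **That a share of 2% to 4% can be set against the 9-point target effect.** It is a share within each arm and nearly the same in both, so it is not a between-arm difference.

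**Conclusion.** The definition is wrong as written, at the lowest severity. The no-anaemia band omits exactly 12.0 g/dL and so is not the complement of the primary definition; that much follows from the text alone.

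The size is an estimate. Literal use would leave about 2% to 4% of women (about 50 to 100 of 2580) without a category in the four-band comparison, about equally in each arm. The range depends on the assumed normal distribution, 0.1 g/dL readings and SD of 1.0 to 2.0 g/dL. The primary outcome, the continuous haemoglobin analysis, the sample size and power do not change, and the between-arm contrast in the categorical table would hardly move.

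**What to change.** In Secondary outcomes, (2) Clinical endpoints, Anaemia, change the no-anaemia band from > 12.0 g/dL to ≥ 12.0 g/dL, and carry the same bands into the analysis plan before unblinding. The four categories are then exhaustive at one decimal, and the no-anaemia band becomes the exact complement of the primary definition. This applies the protocol's own primary threshold and introduces no new one. The cost is one symbol, with no effect on sample size, data collection or the primary analysis.
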